# Cardiac rehabilitation for children and young people (CardioActive): protocol for a single-blind randomised feasibility and acceptability study of a centre-based cardiac rehabilitation programme versus usual care in 11–16 years with heart conditions

**DOI:** 10.1136/bmjopen-2023-077958

**Published:** 2024-02-24

**Keywords:** MENTAL HEALTH, Paediatric cardiology, REHABILITATION MEDICINE

## Abstract

**Background:**

Congenital heart conditions are among the most common non-communicable diseases in children and young people (CYP), affecting 13.9 million CYP globally. While survival rates are increasing, support for young people adjusting to life with a heart condition is lacking. Furthermore, one in three CYP with heart conditions also experiences anxiety, depression or adjustment disorder, for which little support is offered. While adults are offered cardiac rehabilitation (CR) to support their mental and physical health, this is not offered for CYP.

One way to overcome this is to evaluate a CR programme comprising exercise with mental health support (CardioActive; CA) for CYP with heart conditions. The exercise and mental health components are informed by the metacognitive model, which has been shown to be effective in treating anxiety and depression in CYP and associated with improving psychological outcomes in adult CR.

**Method and analysis:**

The study is a single-blind parallel randomised feasibility trial comparing a CR programme (CA) plus usual care against usual care alone with 100 CYP (50 per arm) aged 11–16 diagnosed with a heart condition. CA will include six group exercise, lifestyle and mental health modules. Usual care consists of routine outpatient management. Participants will be assessed at three time points: baseline, 3-month (post-treatment) and 6-month follow-up. Primary outcomes are feasibility and acceptability (ie, referral rates, recruitment and retention rates, attendance at the intervention, rate of return and level of completion of follow-up data). Coprimary symptom outcomes (Strength and Difficulties Questionnaire and Paediatric Quality of Life) and a range of secondary outcomes will be administered at each time point. A nested qualitative study will investigate CYP, parents and healthcare staff views of CR and its components, and staff’s experience of delivering CA. Preliminary health economic data will be collected to inform future cost-effectiveness analyses. Descriptive data on study processes and clinical outcomes will be reported. Data analysis will follow intention to treat. Qualitative data will be analysed using thematic analysis and the theoretical framework of acceptability.

**Ethics and dissemination:**

Ethical approval was granted on 14 February 2023 by the Greater Manchester East Research Ethics Committee (22/NW/0367). The results will be disseminated through peer-reviewed journals, conference presentations and local dissemination.

**Trial registration number:**

ISRCTN50031147; NCT05968521.

STRENGTHS AND LIMITATIONS OF THIS STUDYThe study will evaluate anovel cardiac rehabilitation intervention (CardioActive) for children and young people with heart conditions, which includes both mental and physical health support based on evidenced-based psychological theory.As the study is feasibility, the sample size is limited and the study is not powered to determine efficacy.Data collection will be conducted by researchers blind to participant allocation

## Introduction

Congenital heart disease (CHD) affects 13.8 million children and young people (CYP) under the age of 20 globally.^1^ Survivors of CHD face challenges and comorbidities which impact their ability to function,^2^ future employment and progression into independent adulthood.^3 4^ CYP with heart conditions have a reduced quality of life and poorer psychological functioning,^5–7^ as 41% of CYP with CHD experience significant difficulties adjusting to their heart condition, and 30% experience clinically significant anxiety or depression.^7–13^ In addition, overprotection from parents, educators and healthcare staff contributes to reduced physical activity and exercise intolerance.^14–17^ This is particularly important as sedentary lifestyles are a risk factor for atherosclerosis, cardiovascular disease, obesity and diabetes.^18^

A possible means of improving physical and mental health outcomes would be to facilitate access to a cardiac rehabilitation (CR) programme that improves healthy behaviours such as exercise and psychological self-management skills. CR programmes provide a unique opportunity to improve physical health, provide education around lifestyle and risk factors, and provide psychological support.^19 20^ In the UK, following a cardiac event, adults are encouraged to attend CR programmes, which have been recommended by the National Health Service (NHS),^21^ the Department of Health, National Institute for Health and Care Excellence^22^ guidelines (CG172, CG94 and NG106) and the British Association for Cardiovascular Prevention and Rehabilitation.^23^ In adults, CR programmes have been found to reduce patient mortality, morbidity, hospital readmissions, improve quality of life and be a cost-effective intervention.^24 25^ While CR programmes are accessible for adults, equivalent programmes are not routinely available for CYP living with heart conditions.

Previous systematic reviews and meta-analyses of paediatric CR have indicated that paediatric CR programmes improve physical, developmental, cognitive and psychosocial outcomes.^24 26–28^ Akamagwuna and Badaly^24^ conducted a systematic review of 20 paediatric CR programmes. They found that both home-based and outpatient programmes were associated with improvements in cardiorespiratory outcomes, quality of life and psychosocial functioning. Previous youth CR programmes have predominantly focused on improving physical health outcomes, with less attention given to mental health components, despite 41% of patients struggling with adjusting to living with a heart condition. Tesson *et al*^29^ conducted a systematic review of psychological interventions for childhood-onset heart disease and found only two studies focused on interventions for CYP.^30 31^ However, the results were disappointing, as they did not lower anxiety, depression^31^ or improve quality of life.^30^ CR with CYP could benefit from routine exercise programmes combined with psychological input aimed at improving adjustment and mental health outcomes.

Drawing on the literature on physical and psychological effects of CR techniques in CYP^29–32^ and informed by theory and research on metacognitive therapy (MCT) in adult CR and mental health^33–35^, we have devised CardioActive (CA), a six-session CR package for use with CYP. The duration of the CA programme is briefer than previous programmes where patients have on average received 2.5 sessions per week for 16 weeks.^24 26–28 32^ The physical health component has been informed by recommendations for physical activity in CYP with CHD^36–39^, and the latest systematic reviews and meta-analyses which suggest that programmes should include a combination of endurance and strength-based exercises.^29–32^ The mental health/adjustment component of CA is informed by the metacognitive model^40–42^ of anxiety, depression and stress and focuses on helping CYP to reduce their worry and unhelpful self-monitoring processes. According to the metacognitive model psychological distress and failure to adjust is maintained by a style of thinking termed the cognitive attentional syndrome (CAS). The CAS is characterised by repetitive negative thinking (worry, dwelling), monitoring for threat (ie, checking for symptoms), inflexible attention and engaging with unhelpful coping strategies (ie, avoiding exercise, resting more, poor eating and avoidance). Metacognitive approaches may be more appropriate than cognitive therapy approaches as cognitive therapy uses techniques such as reality testing patient’s thoughts, which in heart disease patients are often realistic (ie, ‘what if my heart disease gets worse?’) and may not be amenable to cognitive therapy techniques.^43^ This approach has been usefully applied in adult CR to improve psychological outcomes.^34^

While the metacognitive approach is promising, further research is needed to understand the views and responses to the metacognitive approach delivered as part of CR for CYP. As such, the aim of the proposed study is to develop a CR programme (CA), which incorporates mental health support for CYP and to evaluate the acceptability and feasibility of the programme in comparison to usual care.

## Methods

### Design

The current study is a parallel single-blind randomised feasibility study in CYP aged 11–16 with a heart condition with 12 and 24 weeks follow-up, comparing routine clinical management (treatment as usual (TAU)) against the CA programme. Qualitative investigation will be embedded within the trial. Preliminary economic data will be obtained to inform the optimum way of evaluating cost-effectiveness in any subsequent definitive trial. See figure 1 for an overview of the trial design according to Consolidated Standards of Reporting Trials (CONSORT) guidelines.^44 45^ The recommendations for the Interventional Trials 2013 Standard Protocol Items: Recommendations for Interventional Trials Checklist^46 47^ is included in Additional file 1. Figure 2 outlines the schedule of recruitment, interventions and assessment.

**Figure 1 F1:**
[figure not shown]
Trial flow diagram.

**Figure 2 F2:**
[figure not shown]
Schedule of events. Schedule of enrolment, interventions and assessments. CHU-9D, Child Health Utility-9D; CR, cardiac rehabilitation; CYP, child and young person rated; ISWT, Incremental Shuttle Walk Test; MCQ-A, Metacognition Questionnaire-Adolescent; P, parent rated; PedsQol, Paediatric Quality of Life; SDQ, Strength and Difficulties Questionnaire; SUQ, Service-Use Questionnaire; 6MWT, 6 min walk test.

### Trial population

The trial population is children and adolescents attending cardiology outpatient services.

### Eligibility criteria

In order to be eligible to take part in the study participants will meet the following inclusion and exclusion criteria:

### Inclusion criteria

Aged between 11 and 16 years.Ability to consent to participate.Native fluency in English language.Diagnosed with at least one of the following: congenital heart disease (all subtypes), cardiomyopathy, cardiac arrhythmia, heart failure, postcerebrovascular event, postheart valve repair/replacement.

Participants will be excluded if they meet one or more of the following:

Presence of significant risk or safeguarding concerns (ie, exercise risk).Head injury/organic impairment.Significant communication and/or social difficulties.

Only patients with a formal diagnosis or under assessment for one of the exclusion criteria will be excluded from the study.

### Recruitment and allocation

Participants will be screened for eligibility during routine clinic appointments by clinicians and/or cardiac team members. Clinicians/cardiac team members will ask eligible patients and their parent/caregiver if they are interested in hearing more about the research study and if their contact details can be passed onto the research team. The research team will then contact eligible and interested patients and their caregivers to provide further information about the study, answer any questions, arrange for consent to be obtained and collect baseline data. Once baseline data have been collected, participants will be randomised to a study arm using sealed-envelope software.^48^ Randomisation (at the individual level) will be independent and concealed, after stratification by age (11–13 and 14–16) and sex (male and female). Within strata, allocation will occur within blocks of size 4 or 6, determined at random and with equal probability by the software. This will minimise future allocation ‘predictability’. A member of the research team not blinded to allocation will contact parents/caregivers to inform them of the allocation within 2 days. Blinding of allocation will be maintained for quantitative research assistants (RAs), and the trial statistician until all outcome measures for all subjects have been collected. The trial executive committee (TEC) will regularly monitor any unblinding’s and corrective action will be implemented if needed.

### Trial conditions

#### CA programme

The programme will consist of six face-to-face group-based sessions lasting up to 90 min of a structured exercise programme with integrated educational and lifestyle modules, and a psychological component delivered at the recruiting hospital sites. Exercise sessions have been reviewed by a physiotherapist with experience working with patients with heart conditions and a child cardiologist who have deemed the exercise safe for CYP to engage in. Patients are free to stop the exercise if they begin to feel unwell. Lifestyle modules will focus on modifiable risk factors. The psychological treatment component (MCT) is integrated throughout each session and focuses on controlling worry and using adaptive attention strategies. Sessions include group discussions, experiential learning and homework tasks that participants are asked to complete between sessions. Participants in this treatment arm will also receive routine clinical outpatient management (TAU) alongside CR.

#### Treatment as usual

TAU will consist of routine clinical outpatient management, routine screening and medication management, which includes a review with their cardiologist or cardiac specialist nurse every 6–12 months, depending on the nature and severity of the heart condition.

#### Staff training and supervision

The intervention will be codelivered by two cardiology staff members. Staff from the cardiology department will receive two full training days in the intervention followed by 6 weeks of supervised practise in delivering the intervention to a pilot group of volunteers. A further workshop will address any challenges the staff’s experienced when delivering the intervention. Staff’s delivery of the intervention will be monitored by listening to audiorecordings of sessions and they will receive supervision throughout the trial. Adherence to the intervention will be assessed using an adherence checklist completed by the staff at each session.

### Data collection

The planned study recruitment date is March 2024, with the end of follow-up marking study completion in June 2025. There will be three follow-up assessment points: baseline, 12 weeks (end of treatment) and 24 weeks (follow-up). To ensure completeness of the questionnaires, participants will be asked to arrange a visit, either at an NHS site or in their own home, at each time point. Participants’ total time involvement in the study will be 24 weeks. Participants will be reimbursed with a £10 shopping voucher for completing each assessment.

### Criteria for discontinuation

Participants may withdraw from the study at any time, without any consequences to themselves, their healthcare or their ability to take part in future research. Participants who withdraw will continue to receive usual care. Participants can also be withdrawn at the request of the chief investigator or cardiology service, but this would only happen if a participant’s life or long-term health or welfare was at risk from continued participation in the study.

### Outcomes

The primary outcomes of the study are feasibility and acceptability outcomes. Feasibility will be assessed using referral rates, recruitment (ie, number of patients consented and randomised, number of patients declined the study) and retention rates (ie, number of patients withdrawn from the study, lost to follow-up) and attendance at the intervention. Qualitative semistructured focus groups or interviews, as preferred, will be used to understand CYP, caregivers and healthcare professionals’ views of acceptability of the intervention and targets for improvement. All outcomes listed below will be obtained at each assessment time point.

### Measures

#### Strength and Difficulties Questionnaire

The Strength and Difficulties Questionnaire (SDQ)^49^ is a behavioural measure completed by the caregiver and child for children aged 2–17. The measure has five subscales: emotion, hyperactivity, conduct, peer relations and prosocial behaviour. Each subscale contains five items, and each item is scored ‘not true’, ‘somewhat true’ or ‘completely true’. Scores for the subscales range from 0 to 10, with total difficulties score (0–40) generated by summing together the scores from all subscales except prosocial. Higher scores on the prosocial scale reflect strengths whereas higher scores across other subscales reflect difficulties.^49^ The SDQ subscales have satisfactory internal consistency (mean Cronbach’s alpha=0.70) and test–retest reliability ranging from 0.75 to 0.91.^50^

#### Paediatric Quality of Life

The Paediatric Quality of Life (PedsQol)^51^ consists of 23 items, which measures health-related quality of life including physical, emotional, social and school functioning, and is commonly used in paediatric cardiology.^5 8^ The items are scored on a Likert scale ranging from 0 (never) to 4 (almost always). Total scores range from 0 to 100, with higher scores indicating better quality of life. The PedsQol will be completed by CYP.

#### Six minute walk test

The 6 minute walk test (6MWT)^52^ is used to assess aerobic capacity and endurance. Participants are asked to walk as far as possible for 6 minutes and the total distance covered during this time is used as the outcome. Performance on the 6MWT has been predictive of morbidity and mortality whereby poorer performance is associated with increased mortality.^52^

#### Incremental Shuttle Walk Test

The Incremental Shuttle Walk Test (ISWT)^53^ is used to assess exercise capacity. The ISWT is a 12-level test (1 min in each level), whereby participants walk up and down a 10 m course with increasing acceleration of 0.17 m/s up to a maximum speed of 2.37 m/s. The walking speed is dictated by an audio signal. The test ends when the subject has a heart rate greater than 85% of their predicted maximum, is limited by dyspnoea, or when the subject is unable to maintain the required speed and does not complete a shuttle for a second consecutive time. The distance covered from the number of shuttles will be calculated.

#### Physical activity monitoring

Participants will wear an accelerometer (Actigraph) for 5 days to monitor physical activity levels at each assessment. Data collected via the Actigraph include total movement, moderate to vigorous physical activity, non-sedentary time, step count and energy expenditure.

#### Metacognition Questionnaire-Adolescent

The Metacognition Questionnaire-Adolescent (MCQ-A)^54^ assesses metacognitive beliefs (beliefs about thinking) across five subscales: uncontrollability and dangerousness of worry, need to control, cognitive self-consciousness, positive beliefs about worry and cognitive confidence. The 30 items are scored on a Likert scale from 1 (do not agree) to 4 (agree very much) with total scores ranging from 30 to 120 and 6–30 for each subscale.^54^ The internal consistency of the MCQ-A across total scores and most subscales have been supported with adequate to excellent Cronbach alphas (0.76–0.92).^55^ This MCQ-A will be completed by CYP.

#### Child Health Utility-9D

The Child Health Utility-9D (CHU-9D)^56^ measures PedsQol using nine dimensions (including worried, sad, pain, tired, annoyed, schoolwork/homework, sleep, daily routine and ability to join in activities) and is suitable for CYP aged between 7 and 17 years. Each item has five levels ranging from no problems to inability to do the item.^56^ The CHU-9D has strong internal consistency (Cronbach’s alpha=0.79) and strong test–retest reliability (interclass correlation coefficients=0.75).^57^ The CHU-9D will be completed by CYP.

#### Demographic information questionnaire

The demographic questionnaire will collect variables including child’s age, sex, weight, height, body mass index, type of heart problem, comorbid mental and physical illnesses, ethnicity, medication, socioeconomic status, parental occupational status. This will be completed by parents/primary caregivers.

#### Health and Social Care Service-Use Questionnaire

The Service-Use Questionnaire will include questions about whether the child has used any primary, secondary or community-based health and social care and how often they used the service in the last 16 weeks (baseline study visit) or since the last assessment (follow-up study visits). The questionnaire will be developed from existing child-relevant service use questionnaires held by the coapplicants and through discussion with the patient and public involvement (PPI) representative, parent advisory group and clinical members of the study team. This will be completed by parents/primary caregivers.

### Qualitative Nested Study

We will investigate patients’, caregivers’ and healthcare professionals’ experiences of the CA programme, targets for improvement, perceived acceptability of components of CR and examine participants experience of living with/managing heart conditions using semistructured interviews with CYP (n=20), caregivers (n=10) and healthcare professionals (n=10). Sampling will be purposive to ensure variation in key variables including age, type of health condition, relationship to CYP and discipline of healthcare professional (eg, physiotherapist, cardiologist, clinical psychologist). We will endeavour to recruit patients with a range of experiences of CR including those for whom engagement has been low as well as those who have attended regularly. We will explore the acceptability of CR, factors influencing participants’ engagement, and barriers and enablers to CR being implemented within services. We will also explore with participants their experiences of key trial processes (eg, outcome measures, recruitment and randomisation procedures) to inform the design of a definitive trial. An interview topic guide will be used in order to maintain a consistent structure. Members from the PPI group will be involved in the development of the interview schedule and piloting for the qualitative interviews. Participants will be reimbursed for taking part in qualitative interviews or focus groups.

### Sample size calculation

Feasibility trials are not powered to provide a definitive effectiveness analysis. Therefore, the sample size is based on having sufficient patients to evaluate the acceptability/feasibility of the intervention (as measured by patient acceptability and adherence ratings, recruitment, and retention rates), and to obtain a provisional estimate of the ‘promise’ of the intervention (eg, an 80% CI) for powering a future definitive randomised controlled trial (RCT). We will recruit 50 patients per arm (total N=100), which would allow for an overall attrition rate of up to 20% to be determined to be within eight absolute percentage points with 95% confidence. The total sample size is in line with recommendations by Lancaster *et al*.^58^ This will also be sufficient to estimate key ‘clinical’ parameters, such as the SD of potential outcomes (in the larger trial), with adequate precision, for which samples of 40 are generally sufficient.^59^

Our qualitative sample has been informed by prior experience and published guidance.^60^ Previous research suggests that a sample size of 12 can achieve data saturation.^61^ The exact number will be determined by data sufficiency, achieving adequate variance in recruitment and thematic saturation, however, we are confident this estimate will be sufficient to answer the relevant research questions.

### Analyses

#### Quantitative analyses

As this is a feasibility study, we will not be carrying out hypothesis testing to determine if the intervention is effective. Instead, descriptive data on study processes and clinical outcomes will be reported. Following an intention-to-treat protocol, we will present data relating to participant recruitment, randomisation, retention at follow-up and drop-out rate in a CONSORT flow chart. The attrition rate will be calculated (with a 95% CI) and reasons for drop-out will be recorded where possible. We will also assess rates of missing data (including which elements) on specific questionnaires and whether any of the measures display floor and/or ceiling effects.

We will summarise by trial arm, as appropriate (eg, mean/SD; median/IQR; proportion/95% CI; data range), data for all potential (ie, for the larger trial) clinical primary outcome measures. We will also report 80% CIs for the trial arm coefficient from appropriate regression analyses (adjusting for age, gender and the corresponding baseline outcome) by way of investigating the promise of the CA programme. This information, the SD of the SDQ and the PedsQoL, the estimated attrition rate and recruitment-based data will be used to help inform the sample size calculation for the large-scale, definitive RCT (in addition to other (published) sources). The statistical analysis plan will be produced by MH (statistician) prior to the examination of outcomes.

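### CA is delivered in groups in one arm only, but neither the adjustments named for the arm-effect regression nor the estimates carried to the definitive trial allow for clustering within those groups

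*Protocol article*

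**What the plan says.** All references are to the Protocol article.

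- Allocation (Recruitment and allocation): "Randomisation (at the individual level) will be independent and concealed, after stratification by age (11–13 and 14–16) and sex (male and female"). Treatment group plays no part in allocation.
- Experimental arm (CA programme): "The programme will consist of six face-to-face group-based sessions lasting up to 90 min", with discussion and shared learning in the group. Under Staff training and supervision, two cardiology staff lead the sessions together.
- Control arm (Treatment as usual): routine outpatient reviews and medication management, with no treatment groups.
- Arm effect (Quantitative analyses): "80% CIs for the trial arm coefficient from appropriate regression analyses (adjusting for age, gender and the corresponding baseline outcome"), offered as evidence of the programme's promise. No hypothesis test is planned.
- Use of the results (Quantitative analyses): the interval, the SDs of the SDQ and PedsQoL, the attrition rate and the recruitment data are to feed the definitive trial's sample size, alongside published sources. A statistical analysis plan (SAP) is to be written before outcomes are examined; it is not available here.
- Size of this trial (Sample size calculation): 50 per arm, justified by an "overall attrition rate of up to 20% to be determined to be within eight absolute percentage points with 95% confidence", and also by the wish for a provisional 80% interval for the effect.

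The article does not mention clustering, an ICC, a group size or a design effect.

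**The concern.** CA participants share a group, its leaders and its discussions over six sessions, so their outcomes may be more alike than those of unrelated participants. Usual-care participants have no such link. A regression with only age, gender and baseline as covariates and ordinary standard errors would treat the 50 CA participants as 50 independent observations. With a positive within-group correlation, the standard error of the arm coefficient would be too small.

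Two uses of the data are exposed. First, the 80% interval is the trial's only inferential statement about clinical effect, and its coverage could fall below the stated level. Second, a feasibility trial exists to supply planning inputs. For a group intervention, group size and a first look at the ICC are among those inputs, and the article's list leaves them out.

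**Working it through.** **The plan's own figure.** Attrition of 20% with N = 100: 1.96 × √(0.20 × 0.80 / 100) = 0.0784, or 7.84 points against the stated 8. Conversely, 8 points needs 1.96² × 0.16 / 0.08² = 96.04, so 97 patients. The stated precision reproduces, and the 100 patients do not rest on the arm effect.

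**Inputs from the document.** n = 50 per arm, equal allocation, a two-sided 80% interval (z = 1.2816), groups in the CA arm only.

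**Assumed inputs.** Members per CA group m = 6, 8 or 10; ICC from 0 to 0.10, taken as the correlation left after covariate adjustment; equal total residual variance in both arms.

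**Formulae**, in residual-SD units:

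- Design effect in the CA arm: DE = 1 + (m − 1) × ICC. In the usual-care arm it is 1.
- 80% half-width allowing for clustering: 1.2816 × √((DE + 1)/n).
- Ratio of the true standard error to the one that ignores groups: √((DE + 1)/2).
- Coverage of an interval that ignores groups: 2Φ(1.2816 / ratio) − 1.
- Multiplier on the patients needed in an equal-arm definitive trial: (DE + 1)/2.

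**Worked case, m = 8, ICC = 0.05.** DE = 1 + 7 × 0.05 = 1.35. Ratio = √(2.35/2) = 1.084. Coverage = 2Φ(1.2816/1.084) − 1 = 76.3%. Multiplier = 2.35/2 = 1.175.

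**Results at 50 per arm.** Ignoring groups, the half-width is 1.2816 × √(2/50) = 0.2563 SD. At ICC 0 nothing changes and coverage is 80%.

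| ICC | m | DE | SE ratio | Half-width allowing for groups (SD) | Coverage if groups ignored | Multiplier |
|---|---|---|---|---|---|---|
| 0.01 | 6 | 1.05 | 1.012 | 0.2595 | 79.4% | 1.025 |
| 0.01 | 8 | 1.07 | 1.017 | 0.2608 | 79.2% | 1.035 |
| 0.01 | 10 | 1.09 | 1.022 | 0.2620 | 79.0% | 1.045 |
| 0.05 | 6 | 1.25 | 1.061 | 0.2719 | 77.3% | 1.125 |
| 0.05 | 8 | 1.35 | 1.084 | 0.2778 | 76.3% | 1.175 |
| 0.05 | 10 | 1.45 | 1.107 | 0.2837 | 75.3% | 1.225 |
| 0.10 | 6 | 1.50 | 1.118 | 0.2866 | 74.8% | 1.25 |
| 0.10 | 8 | 1.70 | 1.162 | 0.2978 | 73.0% | 1.35 |
| 0.10 | 10 | 1.90 | 1.204 | 0.3086 | 71.3% | 1.45 |

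The ratio and coverage do not depend on n, so they are the same with 40 per arm, provided m is the number analysed per group.

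**Simulation check.** With 50 per arm and 20,000 replicates per setting, coverage was 79.3–79.4% at ICC 0.01, 75.1–77.5% at 0.05 and 70.5–75.6% at 0.10, in line with the formula.

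**Illustration for a definitive trial.** With an assumed effect of 0.3 SD, 90% power and a two-sided 5% level, 234 per arm would become 240–245 at ICC 0.01, 264–287 at 0.05 and 293–340 at 0.10.

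**How much this trial can say about the ICC.** Fifty CA participants make 50/10 = 5 to 50/6 ≈ 9 groups, which is too few for a precise estimate.

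**The case against.** The strongest reply is that the article is silent rather than wrong. The regressions are described only as appropriate ones; the bracket lists covariates and does not fix the error structure. A group random effect in the SAP would contradict nothing. A reader might infer that the plan commits to treating all participants as independent, but the text does not say so. That part of the reply stands. It does not remove the point: the article goes as far as naming an adjustment set and a list of planning inputs, and the feature specific to a group intervention is absent from both. An SAP that followed the text as it stands would ignore groups.

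A reader might also infer that the definitive trial's sample size omits a design effect, or that the trial will be underpowered. The document does not support this. That calculation is not made here, and the published sources it is to draw on could supply an ICC.

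The attrition precision is another tempting target. It reproduces as stated, and nothing in the document shows that loss from the study clusters by CA group; under Data collection, participants arrange their own assessment visits at an NHS site or at home. Nor does the article make a case for adding site to the randomisation strata. It does not give the number of sites, and with only two the four strata would become eight for 100 participants in blocks of 4 or 6.

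Finally, the stakes are limited: no test rests on the interval, it is called provisional, and this trial's ICC estimate will be weak. All of that is fair, and it bears on how strongly to press the point rather than on whether it is right.

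**Conclusion.** The point holds in a conditional form. The design is partially nested, and neither the named adjustments nor the listed planning inputs reflect that. If the within-group ICC is positive and the model ignores groups, the 80% interval falls short of its nominal coverage. The loss is trivial at ICC 0.01, where the correct interval is 1–2% wider. It is noticeable at 0.05 (6–11% wider) and material at 0.10 (12–20% wider). At ICC 0 there is no loss. These sizes rest on assumed groups of 6 to 10 and assumed ICCs.

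The multipliers are inflation on the unadjusted sample size and should not be read as the percentage shortfall. At m = 8, a multiplier of 1.175 corresponds to a shortfall of 1 − 1/1.175 = 14.9%, and 1.35 to 1 − 1/1.35 = 25.9%.

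**What to change.** 1. Record a CA group identifier for every CA participant.
2. State, in the protocol or the SAP, that the arm coefficient comes from a partially nested model: a random effect for CA group in the CA arm only, usual-care participants as singletons, the planned adjustment for age, gender and baseline retained, and small-sample degrees of freedom.
3. Report the achieved group sizes and the ICC with its confidence interval for the candidate primary outcomes.
4. Add a design effect to the definitive-trial inputs, calculated over an ICC range that also draws on published values.

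The cost is one database variable, a few sentences and some analysis work. Intervals will be slightly wider. With about 5–9 groups the ICC will be very imprecise, so an estimate near zero should not be read as evidence of no clustering, and external values will still be needed. Neither the treatment nor the 100 patients need change.
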